## Abstract

**Background:**

Delirium is a significant cause of morbidity and mortality among older people admitted to both acute and long-term care facilities (LTCFs). Multicomponent interventions have been shown to reduce delirium incidence in the acute care setting (30–73%) by acting on modifiable risk factors. Little work, however, has focused on using this approach to reduce delirium incidence in LTCFs.

**Methods:**

The objective is to assess the effectiveness of the multicomponent PREPARED Trial intervention in reducing the following primary outcomes: incidence, severity, duration, and frequency of delirium episodes in cognitively impaired residents. This 4-year, parallel-design, cluster randomized study will involve nursing staff and residents in 45–50 LTCFs in Montreal, Canada. Participating public and private LTCFs (clusters) that provide 24-h nursing care will be assigned to either the PREPARED Trial intervention or the control (usual care) arm of the study using a covariate constrained randomization procedure. Approximately 400–600 LTC residents aged 65 and older with dementia and/or cognitive impairment will be enrolled in the study and followed for 18 weeks. Residents must be at risk of delirium, delirium-free at baseline and have resided at the facility for at least 2 weeks. Residents who are unable to communicate verbally, have a history of specific psychiatric conditions, or are receiving end-of-life care will be excluded. The PREPARED Trial intervention consists of four main components: a decision tree, an instruction manual, a training package, and a toolkit. Primary study outcomes will be assessed weekly. Functional autonomy and cognitive levels will be assessed at the beginning and end of follow-up, while information pertaining to modifiable delirium risk factors, medical consultations, and facility transfers will be collected retrospectively for the duration of the follow-up period. Primary outcomes will be reported at the level of intervention assignment. All researchers analyzing the data will be blinded to group allocation.

**Discussion:**

This large-scale intervention study will contribute significantly to the development of evidence-based clinical guidelines for delirium prevention in this frail elderly population, as it will be the first to evaluate the efficacy of a multicomponent delirium prevention program translated into LTC clinical practice on a large scale.

**Trial registration:**

NCT03718156, ClinicalTrials.gov.

## Background

Delirium is a severe neuropsychiatric syndrome with acute onset and a fluctuating course that is characterized by disturbances in cognition, consciousness and attention [1]. It is a significant cause of morbidity and mortality, and is highly prevalent among older individuals across healthcare settings (14–56% reported in acute care [2], 58–75.6% in intensive care units [3], and 1.4–70.3% in long-term care facilities (LTCFs)) [4]. Dementia is an important risk factor for developing delirium among elderly patients [5–7]: the risk of developing delirium is six-times greater among older individuals with dementia when compared to those without the disease [5], and prevalence rates of delirium superimposed on dementia range from 22 to 89% among populations aged 65 and older [8]. This is of particular concern in LTCFs, where dementia is common among the resident population [9]. Residents in LTCFs are also at an increased risk of developing delirium as a function of their frailty, cognitive impairment, and multiple medical comorbidities [10, 11]. Indeed, more than 40% of LTCF residents experience at least one delirium episode over the course of their stay [12], leading to an increased number of falls, accelerated functional decline, increased mortality, and higher healthcare costs [1]. Despite these consequences, delirium recognition is known to be poor. Up to two-thirds of delirium cases are missed by physicians and nurses due to its fluctuant and variable nature [13], ,and it has been reported that 87% of delirium episodes that are superimposed on dementia go undetected in LTCFs [14].

Delirium prevention is essential [15, 16], as the risk of failure to return to baseline among survivors is high, even after adjustment for factors such as age and pre-morbid function [17]. Previous studies have found that 30–40% of delirium cases are preventable with the use of delirium protocols [11], and one American study estimates potential healthcare savings of up to 16 billion dollars annually [18]. Several multicomponent delirium prevention programs (MDPP) have successfully reduced delirium incidence in the acute care setting (30–73% reduction) [1, 18–22]. Independent of type of acute-care ward or unit and level of cognitive decline, a 2015 systematic review of randomized trials of multicomponent interventions reported a relative reduction of 27% (RR 0.73, 95%CI: 0.63–0.85) in delirium incidence [1]. Similarly, a systematic review that analyzed non-randomized studies reported an overall reduction of 63% (RR 0.37, 95% CI: 0.27–0.53) [1]. Such interventions have also been associated with an overall reduction in hospital stay duration and mortality rate [23]. Although the wide range of estimates make it difficult to ascertain the degree to which delirium incidence can be reduced, it is clear that these interventions do have an impact in the acute care setting. The extent to which these findings can be extrapolated to the LTC setting, however, is unknown. For example, the studies listed in the above-mentioned acute care systematic reviews included patients who are younger than LTC residents (average age of 79 in acute care versus 85 in LTC) [1, 18], and who have shorter lengths of stay (average 5–38 days in acute care versus 2.5 years for LTC) [1, 18]. The prevalence of dementia is also different in acute care versus LTC (but this information is not available for the above-mentioned studies).

According to both a 2014 Cochrane Database Systematic Review and the National Institute for Health and Clinical Excellence, research to assess the effectiveness of an MDPP in LTC is urgently needed [24, 25]. Despite this call to action and the increased risk of developing delirium in the LTC population, no multicomponent intervention based on modifiable risk factors had been evaluated and translated into LTC clinical practice to date at the time that we conceived the present trial [19]. However, in 2020, Boockvar et al. published a trial measuring the efficacy of a different multicomponent intervention targeting delirium risk factors (specifically, cognitive impairment, immobility, dehydration, and malnutrition) in LTC, the Hospital Elder Life Program (HELP-LTC) [26]. The HELP-LTC targeted a limited sample size (*n* = 219), and the intervention did not demonstrate its intended effect: no significant differences were found in delirium or delirium severity between the intervention and usual care groups [26]. A multitude of factors are listed by the authors to explain this null finding, including baseline differences in cognitive function between groups, greater than expected improvements on delirium severity and cognition, and novel adaptations of the intervention [26].

In contrast, an integrated knowledge translation strategy [27] was used to develop the PREvention Program for Alzheimer’s RElated Delirium (PREPARED Trial) intervention for use in a LTC setting. Key stakeholders who were familiar with the LTC context were identified early in the research planning process and consulted throughout all subsequent research phases. To address the fact that interventions that are effective in clinical trials may underperform in a real world setting [28], a participatory approach was then used to examine and test the feasibility and acceptability of the PREPARED Trial intervention in two LTC facilities in three 5-week implementation cycles [29]. A thorough evaluation of the effectiveness of the PREPARED Trial intervention in preventing delirium among at-risk LTC residents is now required.

## Study objectives

The primary objective of this study is to compare the efficacy of the PREPARED Trial multicomponent intervention to that of usual care on delirium. Specifically, we aim to assess the effect of the PREPARED Trial multicomponent intervention on the *incidence* of delirium, *severity* of delirium episodes, *duration* of delirium episodes, and *number* of delirium episodes among at-risk, cognitively impaired residents in LTCFs. Our secondary objectives aim to: compare the efficacy of the PREPARED Trial intervention to that of usual care on the *incidence of falls* among cognitively impaired LTC residents; estimate the *association between medication use and delirium incidence* in LTCFs; estimate if there is an effect modification by motor subtype of delirium or by dementia subtype; and measure the prevalence of delirium in participating LTCFs. Finally, we will compare the effect of the multicomponent PREPARED Trial intervention on other health outcomes, including changes in: functional autonomy or social engagement, cognitive functioning, the number of transfers to acute care, the number of consultations with healthcare providers, and mortality rates. All objectives will be reported at the level of intervention assignment.

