Residents will be enrolled based on a series of inclusion/exclusion eligibility criteria. In order to be included, residents must: be 65 years or older; have dementia and/or cognitive impairment, as determined by discussions with the nursing staff and chart abstraction; have a minimum length of stay in the LTC facility of at least 2 weeks prior to the start of the baseline assessments; be at risk of delirium, as indicated by a score of 1 or higher on a validated 5-item delirium risk screening tool [36] (Fig. 2); and be delirium-free at baseline, as assessed by the Confusion Assessment Method (CAM) [37, 38], the Delirium Index (DI) [39], and a brief chart review over a period of two consecutive weeks immediately preceding the start of the follow-up period. Residents will be excluded if they are: unable to communicate verbally (as determined by either the nursing staff or two consecutive 0-score administrations of the composite cognitive interview, which is part of the CAM procedure); unable to communicate verbally in English or French; have a history of specific psychiatric conditions (bipolar disorder, depression with signs of psychosis, and psychotic disorders) or intellectual disability [40, 41]; or are being provided with end-of-life or palliative care.

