### Sample size calculation

Based on sample size calculations, we plan to recruit between 400 and 600 LTC residents in the current study. Sample size was computed for our primary objective, to detect any differences between our intervention and control trial arms in the incidence of a first delirium episode after 18 weeks of follow-up. We used the Freedman log-rank test method to compare two survivor functions at the end of study follow-up. In a post-hoc secondary analysis of the precursor LTC delirium study, for which we applied the PREPARED Trial inclusion and exclusion criteria [33], we obtained incidence rates that we assume will be experienced by our control group, namely 3.75 cases per 100 person-weeks. We tested different scenarios concerning the size of our sample after 18 weeks of follow-up from baseline. We also tested our assumptions regarding the magnitude of our intervention effect by allowing the reduction in incidence rates to vary between 30 and 73%, as previous studies (in non-LTC settings) have reported this range in variation [1, 18–22]. Using methods of estimation ‘uncorrected’ for cluster randomization, we found that including 180 residents per trial arm (after assuming a 15% rate of attrition over our 18 week follow-up period to account for deaths, transfers and drop-outs) will enable us to detect a 40% reduction in the incidence of delirium (HR = 0.6) with a power of 80% at the 5% level (assuming 2-tailed test and equal group size).

The ‘corrected’ sample size for cluster randomization was then computed according to Rutterford et al. (2015) [42], where a design effect was incorporated that inflated the preliminary uncorrected calculation [43]. This design effect depends on two variables: 1) the Intra-cluster Correlation Coefficient (ICC) and 2) the number of clusters, where the total estimated required sample size is directly proportional to the magnitude of ICC and inversely proportional to the total number of clusters participating in the trial. Our sample size analysis, therefore, provides estimates using two conservative values for our expected outcome, and incorporates scenarios for both ICC and the number of clusters (or LTC facilities) that will be included in the study (Fig. 3).

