### Assessments

As part of the eligibility procedure, delirium risk will be assessed using a validated five-item delirium risk screening tool (see “Is the resident at risk?” section of the Decision Tree, Fig. 2) [36]. To be included for study, a resident will require a score of 1 or higher on this scale. Prevalence of delirium will be then assessed weekly for 2 weeks at baseline (screening), and only residents with two consecutive negative CAM scores will be considered for trial inclusion. Delirium incidence and severity (primary outcomes) will be assessed weekly during the 18-week follow-up period. These delirium assessments will be completed using the CAM [37, 38] and the DI [39] as part of a standardized interaction with the resident based on a series of questions adapted using items from various cognitive assessment tools, specifically the Mini-COG (memory) [51–53], Montreal Cognitive Assessment (orientation) and Hierarchical Dementia Scale (concentration) [36, 40, 51, 54, 55]. Functional autonomy will be evaluated at the beginning and end of the follow-up period (weeks 1 and 18) using the Shah version of the Barthel Index [56], an ordinal scale used to measure independence in the activities of daily living (ADLs) adapted to the LTCF environment. Cognitive function will be also be evaluated at these time points using the Hierarchic Dementia Scale (HDS) [55]. Resident comorbidity will be assessed via chart review and reported using the Charlson Comorbidity Index [57] and Geriatric Comorbidity Index [58]. Resident frailty will be assessed via a combination of comorbidity and other measures of well-being, such as functional autonomy, social engagement, and healthcare utilization [59]. Medication information and anticholinergic drug use will also be extracted from resident medical charts, and assessed using the Anticholinergic Burden Scale [60]. Fig. 4 presents a visual representation of the enrolment, intervention, and assessment schedule (SPIRIT Diagram).

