### Statistical data analysis

All statistical analyses will be conducted using SAS version 9.4, STATA version 13.0, and R software. Our study has four primary objectives, four secondary, and six tertiary objectives, all aimed at comparing the effect of our PREPARED Trial intervention to that of usual care. Data analysis will be conducted and reported in accordance with current CONSORT guidelines [61, 62].

For each outcome, we will report the estimates of the regression coefficients obtained from the model for the intervention: Hazard Ratio for survival analysis, beta estimate for the continuous outcome, Incident Rate Ratio for the count outcome, and Odds Ratio for the binary outcome. We will also report the ICC (ratio of the variance explained by the LTCF to the total variance explained by the model). All analyses will be conducted at alpha 0.05 and 95% confidence intervals will be reported.

Missing or incomplete outcome data will inevitably appear in our study. Our general approach will be based on intention-to-treat, using inverse probability weighting to account for missing data [63, 64]. To assess the appropriateness of this approach to missing data, we will conduct two sensitivity analyses using the following approaches: 1) inclusion of subjects with complete data only; and 2) use of multiple imputation for missing data [65, 66].

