## Abbreviations

ACB: Anticholinergic Burden Scale
ANTIPSY: Antipsychotic intervention component of the PREPARED Trial
AVSENS-AUDIT: Hearing intervention component of the PREPARED Trial
AVSENS-VISION: Vision intervention component of the PREPARED Trial
CAM: Confusion Assessment Method
CCI: Charlson Comorbidity Index
CCR: Covariate constrained randomization
CONTEN: Restraint intervention component of the PREPARED Trial
CRN: Clinical research nurse
DI: Delirium Index
DMSS: Delirium Motor Subtype Scale
EDM: Electronic data management
GIC: Geriatric Index of Comorbidity
HDS: Hierarchic Dementia Scale
HELP: Hospital Elder Life Program
HYDRA: Hydration intervention component of the PREPARED Trial
HYDRA++: Hydration plus intervention component of the PREPARED Trial
ICC: Intra-cluster Correlation Coefficient
IMS: Information Management Services, the unit at McGill University/ the Lady Davis Institute of the Jewish General Hospital that will provide the electronic data management platform
LPN: Licensed Practical Nurse
LTC: Long-term care (the study setting)
LTCF: Long-term care facility
MDPP: Multicomponent delirium prevention program
PREPARED: PREvention Program for Alzheimer’s RElated Delirium
PSW: Personal Support Worker
RA: Research Assistant
RISE: Resident Index of Social Engagement
RN: Registered Nurse (or LTCF nurse at a long-term care site)
SBI: Shah version of the Barthel Index
STIMUL: Stimulation component of the PREPARED Trial intervention
TCPS: TriCouncil Policy Statement
TNP: Therapeutic Nursing Plan

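### Motor subtype of delirium is named as an effect modifier, but it arises only after allocation and only in residents who have the primary outcome event

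*Protocol article*

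**What the plan says.** The protocol article, under Study objectives, lists as a secondary aim to "estimate if there is an effect modification by motor subtype of delirium or by dementia subtype". The two subtypes share one clause and one role. No outcome is named for the effect modification. Statistical data analysis describes the primary, secondary and tertiary objectives as "all aimed at comparing the effect of our PREPARED Trial intervention to that of usual care", so the effect in question appears to be that of the intervention.

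Under Participants, freedom from delirium over the two weeks before follow-up is an inclusion criterion. Assessments repeats this: "only residents with two consecutive negative CAM scores will be considered for trial inclusion". The event itself is observed afterwards: "Delirium incidence and severity (primary outcomes) will be assessed weekly during the 18-week follow-up period". The only visible trace of how motor subtype would be measured is an entry in the abbreviation list, "DMSS: Delirium Motor Subtype Scale". The article gives no alternative definition, such as the subtype of an earlier episode.

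**The concern.** An effect modifier must have a value for each participant that does not depend on the treatment or the outcome. Dementia subtype, taken as a characteristic present before randomization, meets that condition. Motor subtype is a property of a delirium episode. Nobody has one at entry, and residents who never become delirious never acquire one. Forming strata on it therefore selects residents by the primary outcome, which the intervention is meant to make rarer. The intervention might also change which subtype occurs, since it includes antipsychotic re-evaluation and removal of restraints during care.

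At stake is the meaning of a published statement that the intervention works better for one motor type than another. Followed as worded, the objective leads either to an interaction that the data cannot identify or to a comparison among cases that randomization no longer protects.

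**Working it through.** **Inputs** (protocol article, Sample size calculation): control rate "namely 3.75 cases per 100 person-weeks", that is 0.0375 per week; hazard ratio 0.6, so 0.0225 per week with the intervention; 18 weeks; two-sided 5% level; 80% power; 15% attrition; Freedman method. Planned enrolment is 200 to 300 per arm.

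**Reproducing the article's own figure.**
- Events: (1.960 + 0.842)² × [(1 + 0.6)/(1 − 0.6)]² = 7.849 × 16 = 125.6, rounded up to 126.
- Delirium-free at 18 weeks under a constant hazard: control exp(−0.0375 × 18) = exp(−0.675) = 0.509; intervention 0.509^0.6 = 0.667.
- Residents: 2 × 126/(2 − 0.509 − 0.667) = 305.9, or 152.9 per arm. Dividing by 0.85 gives 180 per arm, as stated. The inputs and the survival fractions are therefore those the article used.

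**Who has a motor subtype.** With full follow-up, 49.1% of control and 33.3% of intervention residents have a first episode by week 18. The other 50.9% and 66.7% have no subtype. With 200 to 300 per arm that is about 98–147 control and 67–100 intervention cases, or about 83–125 and 57–85 if 15% are simply removed. These cases are then divided among the subtypes.

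**Incidence risk by subtype.** Every resident with a subtype is a case and every non-case has none. Risk within a subtype is 100% in both arms, so an arm-by-subtype interaction on risk has nothing to estimate. This is logic and needs no assumption.

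**Hazard ratio among cases.** This can be computed. For an exponential time cut off at T = 18, the mean time to delirium among cases is 1/λ − T·S/(1 − S), where S is the delirium-free fraction.
- Control: 26.67 − 18 × 0.5092/0.4908 = 8.00 weeks.
- Intervention: 44.44 − 18 × 0.6670/0.3330 = 8.39 weeks.
- Ratio of event rates among cases: 8.00/8.39 = 0.95, against a true 0.6.

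A Cox model restricted to cases gives about 0.93–0.94. Either way the effect nearly disappears, because the residents in whom delirium was prevented have been left out.

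**Severity and duration by subtype.** These compare 49% of one arm with 33% of the other, selected by an event after allocation. An illustrative simulation used inputs that are not in the document: a latent vulnerability raises both the delirium hazard (log-hazard SD 0.5 to 1.0) and severity (correlation 0.5 to 0.8), and the intervention has no effect on severity. The false arm difference within a subtype was about 0.03 to 0.09 SD, against the intervention. When vulnerability raised the hazard of only one subtype and the intervention acted differently on the two (hazard ratios 0.4 and 0.8), the false difference was about 0.08 SD in one and 0.04 SD in the other. This shows that a spurious subtype difference can arise. It does not estimate its size in this trial.

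**Number of episodes by subtype.** Each resident can be given a count for each subtype, zero if never delirious. No selection on the outcome is needed, so this outcome is not affected.

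**The case against.** The strongest defence is that the objective is one clause in a condensed article. It names no outcome, model or interaction term, and the full protocol or analysis plan may handle motor types properly. The clause can be read as asking whether the intervention effect differs across motor types of delirium, which is a sound question. The schedule figure is not shown, so when motor subtype is recorded cannot be seen. Nor is the sentence that all objectives compare the arms strictly accurate: the secondary objectives include delirium prevalence and a medication association.

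Part of this stands. The missing modelling detail is not a fault, and the intended analysis may be a valid one. But that valid reading makes subtype part of the outcome, whereas the clause gives it the same role as dementia subtype. An analysis plan could repair this only by changing what the objective says. Nor is it certain which effect is being modified, but motor subtype would be equally unsuitable as a modifier of the medication association.

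A reader might also infer three stronger things, which the document does not support.
- That no subtype-specific hazard ratio for incidence exists. One among cases can be computed but misleads, and a cause-specific one in all residents is sound.
- That every other outcome is biased. Episode counts by subtype are not affected, and the weakness for severity and duration belongs to any analysis restricted to cases, with or without subtype.
- That a false subtype claim would follow. It could follow; its size cannot be derived from the document and was small under the assumptions tried.

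**Conclusion.** The stated objective gives motor subtype a role it cannot have. This follows from the eligibility rule and the timing of assessments alone. Interaction on incidence risk is not identified, a hazard ratio among cases is drawn from 0.6 to about 0.95, and comparisons of severity or duration within subtype lose the protection of randomization.

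The 51% and 67% without a subtype assume a constant hazard, the planning hazard ratio and full follow-up. They show how many residents fall outside the strata and do not measure bias. The point concerns half of one secondary objective. The primary incidence comparison, the sample size and the dementia-subtype half are sound in this respect. It should be corrected, but it does not threaten the trial's main conclusion.

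**What to change.** Restate the motor-subtype objective as the effect of the intervention on subtype-specific first delirium in all enrolled residents. Treat hyperactive, hypoactive, mixed and unclassified first episodes as competing event types. Report the cause-specific hazard ratio and the cumulative incidence by arm for each type, with a test of equal arm effects across types. Label any comparison of severity or duration by subtype among cases as descriptive. Keep effect modification, as an arm-by-subgroup interaction, for dementia subtype and other baseline factors.

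The cost is a change of wording. No new data are needed, provided motor subtype is recorded at the first episode, which the visible text does not confirm. The downside is fewer events per type, hence wider intervals and limited power for the test of equal effects: the 98–147 control and 67–100 intervention cases expected with full follow-up would be shared among the types.
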